## Abstract

**Background:**

The morbidity of knee arthritis is increasing among aged people and total knee arthroplasty has been its mainstream treatment to date. Postoperative rehabilitation is an important part of the procedure. However, the intense pain during the functional exercise involved has always been a challenge for both patients and health care professionals. The aim of this study is to test the analgesic effect of a mixture of nitrous oxide/oxygeb (1:1) inhalation for patients who are doing functional exercise 1 month after total knee arthroplasty.

**Methods/design:**

This double-blind, randomized, placebo-controlled study will be implemented in the Rehabilitation Department in the General Hospital of Ningxia Medical University. Patients aged between 50 and 75 years who underwent a primary unilateral total knee arthroplasty are eligible for inclusion. The key exclusion criteria include: epilepsy, pulmonary embolism, intestinal obstruction, aerothorax. The treatment group (A) will receive a pre-prepared nitrous oxide/oxygen mixture plus conventional treatment (no analgesics), and the control group (B) will receive oxygen plus conventional treatment (no analgesics). Patients, physicians, therapists, and data collectors are all blind to the experiment. Assessments will be taken immediately after functional exercise begins (T0), 5 min (T1) after functional exercise begins, and 5 min after functional exercise has finished (T2). Patients will be randomly allocated between a treatment group (A) and a control group (B) in a ratio of 1:1. Primary outcome, including pain severity in the procedure, will be taken for each group. Secondary outcomes include blood pressure, heart rate, oxygen saturation, side effects, knee joint range of motion, Knee Society Score (KSS), rescue analgesia need, and satisfaction from both therapists and patients.

**Discussion:**

This study will focus on exploring a fast and efficient analgesic for patients who are doing functional exercise after total knee arthroplasty. Our previous studies suggested that the prefixed nitrous oxide/oxygen mixture was an efficacious analgesic for the management of burn-dressing pain and breakthrough cancer pain. The results of this study should provide a more in-depth insight into the effects of this analgesic method. If this treatment proves successful, it could be implemented widely for patients doing functional exercise in the rehabilitation department.

**Trial registration:**

ChiCTR-INR-17012891. Registered on 6 October 2017.

**Electronic supplementary material:**

The online version of this article (10.1186/s13063-019-3472-7) contains supplementary material, which is available to authorized users.

## Background

Knee arthritis is a chronic joint disease that leads to considerable morbidity in terms of pain, difficulties in performing daily life activities, sleep disorder, functional limitations, mental illness, and decreased quality of life [1, 2]. Knee surgery, including total knee arthroplasty (TKA), for the condition has become increasingly common in developed countries, where it has been influenced a large quantity of aged people occupies 75%. Clinically, TKA is a successful procedure, which is frequently used to bring patients pain relief, improved knee function and quality of life [3, 4]. TKA is associated with damaging postoperative pain that may affect patients’ satisfaction and return to normal function. After TKA surgery, the patients suffer from pain, swelling, restricted blood circulation and a sudden impairment of motor function. Pain levels are consistently reported as higher than other surgical procedures, and are important factors that may influence patients’ willingness to fully engage in rehabilitation activities, which eventually impacts on surgical outcomes [5]. A quick return to normal function after TKA is a desirable outcome for patients, their family members and caregivers. Delayed recovery prevents a prompt return to work and normal activity and increases health care costs [6]. Early mobilization after TKA has been reported to reduce the incidence of complications such as pulmonary embolism, deep vein thrombosis, chest infection, and urinary retention [7, 8], and result in a quicker discharge which could potentially decrease the risk of nosocomial infection [8].

Rehabilitation after TKA generally begins immediately after surgery and, therefore, sufficient analgesia is important. An ideal analgesia for post-TKA rehabilitation will permit adequate knee flexion with minimal pain and without motor impairment, leading to successful mobilization [9]. In China, the development of pain management has lagged that of other countries and has mainly focused on traumatic and acute pain; pain in rehabilitation is not adequately recognized and physicians pay more attention to functional exercise and recovery during the process. Pain relief in rehabilitation post TKA remains a clinical challenge. Patients are required to endure the severe postoperative pain. However, pain-related fear of movement can affect a patient’s functional outcomes [5]. It is hoped that this article provides information that can be used immediately to improve a patients’ experience and outcomes.

Orally administered analgesics are often the main treatment in the immediate- to short-term postoperative period. Despite the effectiveness of opioids, they often lead to some undesirable side effects such as vomiting, constipation, and respiratory depression [10]. It is reported that continuous femoral nerve block (CFNB) with local anesthetics could provide superior analgesia and fewer side effects compared with systemic opioids, thus promoting exercises to increase the knee’s range of motion. Nevertheless, a drawback of CFNB is that it can cause a temporary, reversible weakness that accentuates that already caused by TKA and a subsequent increased risk of falling, thus delaying the ability to move [10, 11]. Nitrous oxide, which has been known as an analgesic gas for more than two centuries, is an effective, fast, safe, and noninvasive form of pain relief in the rehabilitation of patients. Different trials have confirmed that the use of nitrous oxide/oxygen can lead to obvious pain relief in different areas of medicine such as labor, colonoscopy, percutaneous liver biopsy, transrectal biopsy of the prostatic gland, migraine, skin laceration repair, venous cannulation, and dentistry [12–18]. The working mechanism of nitrous oxide/oxygen reported by Emmanouil et al. and Carbajal et al. [19, 20] is that it can stimulate neuronal release of endogenous opioid peptides and activate opioid receptors, aminobutyric acid type A (GABA), and noradrenergic pathways. The anxiolytic and sedative effects resemble those of benzodiazepines. Nitrous oxide hardly dissolves in blood and cannot bind to hemoglobin, acts swiftly and is metabolized by the lungs after inhalation ceases [21]. In 1961, Tunstall developed a stable mixture of nitrous oxide and oxygen for pain relief during childbirth. The two gases were mixed in equal proportions and stored in a single cylinder [22]. Soon, the analgesic use of this gas mixture spread over other settings, such as the dental office, prehospital emergencies, etc. In France, the gas mixture was used only in prehospital care and in some labor rooms, and later in procedure-related pain for children [23]. The mixture could play the same role as at least a 15-mg dose of morphine given intramuscularly [16]. It has been observed that all side effects (nausea, vomiting, dizziness) were transient and vanished within 5 min after removing the inhalation device. No serious side effects were noted [23]. However, this new kind of analgesic has not been accepted all over the world. It is mainly used in developed regions including Britain, Australia, and South Africa. In China, it was firstly used in obstetrics, and later in burns surgery [24]. The apparatus is cheap and portable, but most important is that it is easy for patients to control the device. However, its use in TKA postoperative exercise pain control is rarely reported. This study postulates that a nitrous oxide/oxygen mixture can alleviate the pain level to a certain degree, though not absolutely eliminate the pain of rehabilitative exercise.

## Methods/design

### Patient and Public Involvement

Research questions are based on the PICOS (Population, Intervention, Comparison, Outcome, and Study design) approach:Population: patients who undergo total knee replacement and are do functional exerciseIntervention: nitrous oxide/oxygen inhalationComparison: oxygen inhalationOutcome: pain severity, adverse events, satisfaction from both patients and therapists, Knee Society Score (KSS), the time for ROM ≥ 90° and rescue analgesiaStudy design: a randomized controlled trial (RCT) (Additional file 1)

Potential participants for the study will be sourced from the General Hospital of Ningxia Medical University, which is the biggest general hospital in Ningxia. Recruitment sources will be focused on patients who undergo TKA and are doing functional exercise. A member of the research team will contact the principals, directors, case managers and other relevant staff for information about the study. Should they wish their organization to cooperate with the study, staff members will be asked to provide written information to individual members whom they deem to be an appropriate candidate for the study. If that member or client is interested in participating, based on the information provided, they will then voluntarily contact the research team. Alternatively, should the potential participant wish to be contacted directly by a member of the research team, they may choose to complete a “consent to contact” form. At this point, it is made clear that patients are only consenting to the research team contacting them to discuss the possibility of participating in the study as opposed to actually consenting to participate in the study itself. Those who agree to contact the research team will be invited to attend a screening interview to see whether they meet the inclusion criteria (see Table 1). Moreover, the eligible patients will be informed that they do not need to conduct and assess the outcomes, and the specialized researchers will finish these. To maximize participant access, the study will also be advertised via posters. At the time of consent, all study participants will be invited to indicate whether they wish to receive a summary of the findings or not. A written lay summary will be produced and sent to participants. For acknowledging the time and value of participation, participants will be offered a modest reimbursement (for any time and inconvenience associated with participation in the study). The two gases will be offered free for the participants and small “thank you” gifts will also be given.

**Table 1 Tab1:** Key inclusion and exclusion criteria

Inclusion criteria	Exclusion criteria
Patients underwent primary unilateral total knee replacement	Mental disorder
Age between 50 and 75 years	Drug dependence and drug abuse
Informed and willing to participate in the study	Unconscious and have difficulty in expressing pain by a NRS
Without any postoperative complication	Epilepsy, pulmonary embolism, intestinal obstruction, aerothorax
Recent worst pain (during functional exercise) reported to be 4 or higher (on a Numerical Rating Scale (NRS) of 0 to 10)	Disease involving ear, nose, larynx, such as sinuses, otitis media

### Study design

This double-blind, randomized, placebo-controlled clinical trial aims to determine the analgesic effect of the premixed nitrous oxide/oxygen used in the rehabilitation department for patients who undergo TKA (1 month after TKA). The study will be conducted in the rehabilitation department of the General Hospital of Ningxia Medical University. Patients in the intervention group will receive conventional analgesic regimens (no analgesic) with the premixed nitrous oxide/oxygen mixture inhalation while patients in the control group will receive conventional analgesic regimens (no analgesic) and oxygen inhalation when doing functional exercise (Fig. 1).

**Fig. 1 Fig1:**
[figure not shown]
Study design framework. *TKA* total knee arthroplasty, *NRS* Numerical Rating Scale; KSS Knee Society Score, *ROM* range of motion. Physiological indices include blood pressure (BP), oxygen saturation (SPO_2_), heart rate (HR)

### Study setting and participants

The study will be implemented in the General Hospital of NingXia Medical University, which is a specialized tertiary hospital. A written informed consent form will be collected from all the participants after a thorough explanation of the procedure by the therapists. The researchers state that voluntary participation and all their demographic data and survey answers will be kept confidential. Patients are eligible if they are undergoing primary unilateral TKA (see Table 1). They are ineligible if they are unconscious, or presented with any of the following contraindications to the inhalation of the mixture (hemodynamic instability, vitamin B_12_ deficiency, intracranial hypertension, pneumothorax, intestinal obstruction, epilepsy, pulmonary embolism or facial fractures) [25]. The patients will be randomly allocated to inhale either premixed nitrous oxide and oxygen (intervention group) or oxygen (control group). The medical group and the patients will be all unaware of the mixture inhaled.

### Randomization and blinding

According to the computer-generated random number table in a 1:1 ratio, all the participants will be randomized to the intervention group (conventional treatment plus nitrous oxide/oxygen) or the control group (conventional treatment plus oxygen). The allocation sequence of each patient will be decided by a computer-generated schedule, which will be numbered by a statistician. The randomization schedule will be kept and sealed in an independent research room. Apart from the project manager, who is responsible for gas distribution, no other nurses or data collectors will have access to the data allocation. Prior to, and during, the treatment period, the participants, therapists, and the investigators will all be blind to the allocation. Only the project manager will know the allocation. The two gases will be stored in identical-looking canisters labeled A and B (Additional file 2). Patients given the letter A will be treated using a canister with the appropriate letter containing premixed nitrous oxide/oxygen. Those with letter B will be given oxygen only.

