### Procedure

All the procedures will be carried out in the rehabilitation department. All the patients will be recruited on the basis of being without any other analgesic before this study. The patients will inhale the premixed nitrous oxide/oxygen or placebo gas through a close-fitting mask for 2 min before exercise and throughout the whole process. They will be continuously monitored with a pulse oximeter during the whole process, and blood pressure will be taken before, during and after each functional exercise session. The inhaled mixture will be administered by the patients themselves (Fig. 2). Neither the therapists nor the patients know which gas mixture will be contained in each gas holder. During the functional exercise, the patients will inhale the gas mixture continuously. The inhalation of the gas mixture will be stopped when the functional exercise ends.

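### One fixed canister letter per arm, with its meaning stated in the protocol, leaves the double blind unprotected by design

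*Protocol article*

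**What the plan says.** Under Randomization and blinding, the protocol article describes the gas supply: "The two gases will be stored in identical-looking canisters labeled A and B". It then gives the meaning of each letter: "Patients given the letter A will be treated using a canister with the appropriate letter containing premixed nitrous oxide/oxygen", and "Those with letter B will be given oxygen only". The abstract (Methods/design) uses the same key, calling the nitrous oxide arm group A and the oxygen arm group B.

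The blinding claims stand beside this. Randomization and blinding says that "the participants, therapists, and the investigators will all be blind to the allocation" before and during treatment, and adds: "Only the project manager will know the allocation". Procedure says: "Neither the therapists nor the patients know which gas mixture will be contained in each gas holder". The allocation schedule is sealed away in a separate room, and the project manager distributes the gas.

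The primary outcome is pain on a 0 to 10 numerical rating scale (NRS), rated by the patient (Measures; Primary outcome). Satisfaction on a 5-point scale is rated by patients and therapists and is a secondary outcome. The planned total is 140 patients, allocated 1:1.

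**The concern.** Canisters that look alike hide the gas only if the label does not give it away. Here the label is one letter shared by a whole arm, and the protocol says which gas each letter stands for. That creates two separate weaknesses.

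- **The key is written down.** A person who knows the protocol or its abstract and sees the letter knows the arm. Investigators are listed among the blinded, and they are the people most likely to know the protocol.
- **The code is shared.** Even someone who has never seen the key can work it out from one telling event. From then on the letter identifies the gas for every other patient whose letter that person sees.

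The outcomes at stake are subjective. A patient who believes the gas is active may report less pain, and a therapist who believes it may rate satisfaction higher. The trial's description as double-blind and placebo-controlled is meant to rule this out.

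**Working it through.** The plan gives no figure on blinding to reproduce, so the main check sets its statements side by side.

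**Step 1. What the letter carries.** There are two labels and two gases, and the mapping is stated for both letters under Randomization and blinding and repeated in the abstract. The letter is therefore equivalent to the arm. The shown text describes no patient-specific or scrambled numbering.

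**Step 2. Who is said not to know.**

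| Group | Claim in the article | Does the labelling secure it? |
|---|---|---|
| Investigators | Blind | No, if they know the protocol and see a letter |
| Therapists | Blind; do not know the contents | Only while the key is withheld and no letter is decoded |
| Patients | Blind; do not know the contents | Same condition |
| Project manager | The only person who knows | True only if nobody else combines letter and key |

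The claims and the labelling can coexist only if the key stays away from everyone who sees a letter and no letter is ever inferred. The article describes no step that secures either condition at the canister.

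**Step 3. Are telling events foreseeable?** Yes, from the article itself. Background describes sedative effects of the mixture, and reports that nausea, vomiting and dizziness clear within 5 min of removing the device. Adverse effects and emergency measures lists hallucination among the events to be recorded.

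**Step 4. How far one decoded letter reaches.** With two letters, knowing one gives the other by elimination. The reach is every patient whose letter is seen by the person who decoded it, with a ceiling of 140. With patient-specific numbers, an event in one patient reveals that patient only.

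**Step 5. Illustration of the contrast.** Assume that each patient independently has probability q of an event that reveals the gas. The documents do not give q, so a range is shown. The chance of at least one such event among n patients is 1 − (1 − q)^n. The expected number revealed under patient-specific numbers is nq. The table uses n = 140 (all patients) and n = 140/2 = 70 (if only nitrous oxide patients can show telling effects).

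| q | At least one, n = 140 | Expected, 140q | At least one, n = 70 | Expected, 70q |
|---|---|---|---|---|
| 1% | 1 − 0.99^140 = 76% | 1.4 | 1 − 0.99^70 = 51% | 0.7 |
| 2% | 1 − 0.98^140 = 94% | 2.8 | 1 − 0.98^70 = 76% | 1.4 |
| 5% | 1 − 0.95^140 = over 99.9% | 7 | 1 − 0.95^70 = 97% | 3.5 |

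Even a small q makes one telling event more likely than not. This shows how the two labelling schemes differ. It does not estimate what will happen, and it says nothing about bias in NRS points.

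**The case against.** The strongest defence is that the article contains real safeguards. The schedule is sealed, one person distributes the gas, the canisters look alike, and the text says outright that therapists and patients do not know the contents. A/B labels are compatible with that if the key is kept from patients and site staff. Telling journal readers what A means does not show that anyone on site was told.

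This stands, and it limits the point. A reader might infer that the blind is already broken, or that the blinding statement cannot be true. The documents do not support that. They do not say that patients, therapists or data collectors had the key, that the patient holds the labelled canister, or that data collectors see the label. The figure of the procedure and Additional file 2 are not shown. Speaking of patients as given a letter makes it a fair inference that they see it, but no more than that.

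A reader might also infer that one reveal unblinds all 140 patients. That is a ceiling. A reveal cannot change ratings already recorded, and it affects another patient's pain score only if the knowledge reaches that patient, directly or through staff. The route through staff is strongest for therapist satisfaction, a secondary outcome.

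Finally, it is tempting to express the bias as a share of the detectable NRS difference. The article gives neither a standard deviation nor an expectation effect, so such a figure would be one assumption divided by another.

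The defence does not reach the labelling itself. A sealed schedule and matching exteriors do not conceal what a fixed letter means once its meaning is written in the protocol.

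**Conclusion.** The point holds as a weakness in a stated procedure, not as a missing detail. One disclosed letter per arm leaves the claimed blind of patients, therapists and investigators unprotected by design, and it sits badly with the statement that only the project manager knows the allocation.

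Its reach is bounded: one decoded letter can expose the gas of every other patient whose letter is seen, at most all 140. The conclusion rests on blinded persons being able to see the letter, which is plausible but not stated. It does not rest on the illustrative values of q. Whether unblinding occurs, and how far it would shift pain or satisfaction scores, cannot be determined from the document.

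**What to change.** Replace the letters A and B with a unique canister number for each patient, drawn from the schedule that the statistician already prepares. Let only the project manager, who already distributes the gas, hold the list linking number to gas. Use neutral group codes in the case report forms and dataset, and remove the A/B key from documents that site staff can read.

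The cost is relabelling, a longer key list and slightly more work at gas distribution. No new role is needed.

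The change stops one patient's reveal from decoding the others. It does not stop a patient from recognising the gas by its own effects, and the report should say so. A question at the end of the session on which gas patient and therapist think was given is optional, because it measures blinding and does not protect it.

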### Procedure

All the procedures will be carried out in the rehabilitation department. All the patients will be recruited on the basis of being without any other analgesic before this study. The patients will inhale the premixed nitrous oxide/oxygen or placebo gas through a close-fitting mask for 2 min before exercise and throughout the whole process. They will be continuously monitored with a pulse oximeter during the whole process, and blood pressure will be taken before, during and after each functional exercise session. The inhaled mixture will be administered by the patients themselves (Fig. 2). Neither the therapists nor the patients know which gas mixture will be contained in each gas holder. During the functional exercise, the patients will inhale the gas mixture continuously. The inhalation of the gas mixture will be stopped when the functional exercise ends.

